#### 8.3.1.2. Questionnaires During Treatment Period

##### 8.3.1.2.1 Graded Chronic Pain Scale

This scale captures disability, pain intensity (high and low impact), and whether an individual is able to work due to pain.^26^ GCPS includes, in addition to the 3 items for pain intensity and 4 items for function, one item for number of days of pain. Each item has a score of 0-10. Characteristic Pain Intensity (CPI): compute mean of items 2-4 (pain right now, worst pain, average pain), and multiply by 10. Interference Score: compute mean of items 6-8 (daily activities, social activities, work activities), and multiply by 10. Disability score for number of days with interference: assign points based on below table. Disability score for the interference score: assign points based on **Table 2**.

**Table 2. Rating scale of disability points**

| **Points for Disability Days** | | **Points for Pain-related** | |
| --- | --- | --- | --- |
| 1 month（30 days） | | Interference Score | |
| Days | Points | Interference | Points |
| 0-1 | 0 | 0-29 | 0 |
| 2 | 1 | 30-49 | 1 |
| 3-5 | 2 | 50-69 | 2 |
| 6+ | 3 | 70+ | 3 |

The total Disability Score=Points for Disability Days + Points for Interference Score.

Determination of graded chronic pain status based on CPI and Disability Points. The Specific details based on **Table 3**.

If one or more responses are missing among items 2-4 (pain intensity), the respective subscale should not be scored due to the broad scope that the three items cover. For the function items (6-8), one missing value may not represent the same information loss, and the subscale score could be computed albeit with decreased reliability. Missing data for number of disability days precludes determination of graded chronic pain status.

**Table 3. Determination of chronic pain grade**

| **Grade** | **Label** | **CPI** | **Disability Points** |
| --- | --- | --- | --- |
| 0 | None | 0 | N/A |
| 1 | Low intensity pain, with none-low pain-related disability | <50 | <3 |
| 2 | High intensity pain, with none-low pain-related disability | ≥50 | <3 |
|  | [2a]High intensity pain, without pain-related disability | ≥50 | <3 |
|  | [2b]High intensity pain, with low pain-related disability | ≥50 | <3 |
| 3 | Moderately limiting | N/A | 3-4 |
| 4 | Severely limiting | N/A | 5-6 |

##### 8.3.1.2.2. JFLS-20

The JFLS-20 is an organ-specific instrument comprising 3 constructs for assessing functional status of the masticatory system; the 3 scales exhibit properties that are ideal for both research and patient evaluation in patient groups with a range of functional limitations of the jaw.^27^ The 20-item JFLS covers activities involving social aspects such as facial expressions (happy and angry), kissing, singing, frowning, laughing, and other jaw activities such as chewing a hard bread, chewing crackers, eating soft food that requires no chewing, opening the mouth wide to bite an apple or a sandwich, and talking. A response scale used 0 to 10 signifying degree of limitation (0=no limitation and 10=severe limitation); an option for “not applicable” is also available, and is scored as “missing.” The subscales are computed as the mean response for all items in the subscale. Mastication is based on 6 items, vertical jaw mobility is based on 4 items, and verbal and emotional expression is based on 8 items; 2 items are not scored as part of these 3 subscales. A total score is also computed from the 3 subscales when all 3 component scores are available. The JFLS-20 is designed based on item response theory, and consequently identical non-zero responses to all items within a subscale are highly improbable; non-zero responses that are the same within a subscale were regarded as invalid and recoded to “missing.”

Scoring:

From either the short form (all items) or the long form (items 1, 3, 6, 10, 11, 12, 13, and 19), a single global score of “jaw functional limitation” can be computed as the mean of the available items. Subscale scores for each type of functional limitation are computed, as follows:

Mastication: mean of items 1-6.

Vertical jaw mobility: mean of items 7-10.

Verbal and emotional expression: mean of items 13-20.

A second type of global score can be obtained from the long form by computing the mean of the 3 subscale scores, as computed above. Note that all 3 subscale scores must be present in order to compute the global score in this manner.

For the JFLS-20, scores can be computed based on no more than the following number of items with missing response: short form, 2 items missing allowed; mastication, 2 items missing allowed; mobility, 1 item missing allowed; and communication, 2 items missing allowed. Norms have not yet been established for this instrument.

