**8.2.3 Facial Disability Index (FDI)**

Evaluation and application of the assessment tools were performed by an examiner. The clinical examination followed all biosafety recommendations, and the entire evaluation lasted approximately 40 minutes in a room exclusively reserved for this purpose.

Pain-free opening and maximum unassisted opening are measured by the interincisal distance between the maxillary and mandibular reference teeth. In certain settings, repeating the test, if the pain-free opening if less than 30 mm, might be appropriate in order to assess for possible low-range outlying values. Ask the patient about any pain produced by measuring maximum unassisted jaw opening.

Maximum assisted jaw opening is examiner-based. The examiner uses moderate pressure, push the mouth open further, measures the interincisal distance between the maxillary and mandibular teeth. The examiner has the option of repeating the procedure if she/he believes the patient prematurely terminated the procedure or responded with resistance. If patient indicates to the examiner that the procedure should be stopped, (Yes) is endorsed. If the patient indicates for the procedure to be terminated simultaneous with the examiner’s percept that the assisted opening has reached its maximum, (No) should be endorsed. For all other situations, (No) should be endorsed.

Lateral excursive measurements are made between the maxillary and mandibular reference midlines, while protrusive excursive measurement is made between the labial surfaces of the maxillary and mandibular reference teeth. If the patient cannot perform a movement, indicate this on the recording form by leaving the section blank. For the lateral excursive movements, if the patient is confused about direction she/he should move his or her jaw, touch the ipsilateral side of the face, lip, or even shoulder, and ask the patient to move towards the indicated side. Ask patient to move the mandible forward. Record any reported pain. Note that if the mandibular incisors cannot be protruded beyond the maxillary incisors, the value will be negative. If the incisors exhibit a Class III (anterior cross-bite situation exists) situation in maximum closure, the horizontal overlap is recorded as a negative value. The protrusive movement measured as the distance from the labial surfaces of the maxillary to mandibular incisors, will be recorded as a positive number.

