##### 8.3.1.2.4. Pittsburgh Sleep Quality Index (PSQI)

PSQI aims to assess a person’s sleep quality with questions relating to their sleeping habits within the past month. The PSQI consists of 18 self-rated questions and five questions raised by the bedpartner or roommate **(Table 4)**. The latter five questions are used for clinical information only, are not tabulated in the scoring of the PSQI. These 19 items are grouped into seven component scores, each weighted equally on a 0-3 scale. Higher scores indicate worse sleep quality. These components are subjective sleep quality, sleep latency, sleep duration, habitual sleep efficiency, sleep disturbances, use of sleeping medications, and daytime dysfunction over the past month. The seven-component scores are added in order to obtain a “global” score ranging from 0 to 21 points, where “0” indicates no difficulty and “21” indicates major difficulties in all areas. The global PSQI score, ranging from 0 to 21, can be collected by summing the seven components after weighting them on a scale ranging from 0 to 3. For each component, as well as the global PSQI score, higher sleep scores show worse sleep quality. The global score < 5 associated with good sleep quality while > 5 associated with poor sleep quality.

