**Table 4. Scoring rule of pittsburgh sleep quality index**

| **component1**  **PSQISLPQUAL** | **OVERALL SLEEP QUALITY** | **Q6**  **Minimum Score = 0 (better); Maximum Score = 3 (worse)** |
| --- | --- | --- |
| component2 PSQILATEN | SLEEP LATENCY | **First, recode Q2 into Q2new thusly:**  IF Q2 > 0 and < 15, THEN set value of Q2new to 0  IF Q2 > 15 and < 30, THEN set value of Q2new to 1  IF Q2 > 30 and < 60, THEN set value of Q2new to 2  IF Q2 > 60, THEN set value of Q2new to 3  **Next**  IF Q5a + Q2new = 0, THEN set value to 0  IF Q5a + Q2new > 1 and < 2, THEN set value to 1  IF Q5a + Q2new > 3 and < 4, THEN set value to 2  IF Q5a + Q2new > 5 and < 6, THEN set value to 3  Minimum Score = 0 (better);  Maximum Score = 3 (worse) |
| component3  PSQIDURAT | DURATION OF SLEEP | IF Q4 > 7, THEN set value to 0  IF Q4 < 7 and > 6, THEN set value to 1  IF Q4 < 6 and > 5, THEN set value to 2  IF Q4 < 5, THEN set value to 3  Minimum Score = 0 (better);  Maximum Score = 3 (worse) |
| component4  PSQIHSE | SLEEP EFFICIENCY | Diffsec = Difference in seconds between day and time of day Q1 and day Q3  Diffhour = Absolute value of diffsec / 3600  newtib =IF diffhour > 24, then newtib = diffhour – 24  IF diffhour < 24, THEN newtib = diffhour  (NOTE, THE ABOVE JUST CALCULATES THE HOURS BETWEEN GNT (Q1) AND GMT (Q3))  tmphse = (Q4 / newtib) * 100  IF tmphse > 85, THEN set value to 0  IF tmphse < 85 and > 75, THEN set value to 1  IF tmphse < 75 and > 65, THEN set value to 2  IF tmphse < 65, THEN set value to 3  Minimum Score = 0 (better); Maximum Score = 3 (worse) |
| component5  PSQIDISTB | SLEEP DISTURBANCE | IF Q5b + Q5c + Q5d + Q5e + Q5f + Q5g + Q5h + Q5i + Q5j (IF Q5JCOM is null or Q5j is null, set the value of Q5j to 0) = 0, THEN set value to 0  IF Q5b + Q5c + Q5d + Q5e + Q5f + Q5g + Q5h + Q5i + Q5j (IF Q5JCOM is null or Q5j is null, set the value of Q5j to 0) > 1 and < 9, THEN set value to 1  IF Q5b + Q5c + Q5d + Q5e + Q5f + Q5g + Q5h + Q5i + Q5j (IF Q5JCOM is null or Q5j is null, set the value of Q5j to 0) > 9 and < 18, THEN set value to 2  IF Q5b + Q5c + Q5d + Q5e + Q5f + Q5g + Q5h + Q5i + Q5j (IF Q5JCOM is null or Q5j is null, set the value of Q5j to 0) > 18, THEN set value to 3  Minimum Score = 0 (better);  Maximum Score = 3 (worse) |
| component6  PSQIMEDS | NEED MEDS TO SLEEP | Q7  Minimum Score = 0 (better);  Maximum Score = 3 (worse) |

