| component7  PSQIDAYDYS | DAY DYSFUNCTION DUE TO SLEEPINESS | IF Q8 + Q9 = 0, THEN set value to 0  IF Q8 + Q9 > 1 and < 2, THEN set value to 1  IF Q8 + Q9 > 3 and < 4, THEN set value to 2  IF Q8 + Q9 > 5 and < 6, THEN set value to 3  Minimum Score = 0 (better);  Maximum Score = 3 (worse) |
| PSQI | TOTAL | DURAT + DISTB + LATEN + DAYDYS + HSE + SLPQUAL + MEDS  Minimum Score = 0 (better);  Maximum Score = 21 (worse)  Interpretation:  TOTAL < 5 associated with good sleep quality  TOTAL > 5 associated with poor sleep quality |

Note: PSQISLPQUAL=PSQI sleep quality; PSQILATEN=PSQI sleep latency; PSQIDURAT=PSQI duration of sleep; PSQIHSE=PSQI sleep efficiency; Diffsec=difference in seconds; Diffhour=Difference in hours; GNT=gone to bed at night time; GMT=get up in the morning time; tmphse= time of sleep efficiency; PSQIDISTB=PSQI sleep disturbance; PSQIMEDS=PSQI need medicine to sleep; PSQIDAYDYS=PSQI day dysfunction due to sleepiness; DURAT=duration; DISTB=disturbance; LATEN=latency; DAYDYS=day dysfunction; HSE=sleep efficiency; SLPQUAL=sleep quality; MEDS=medicine to sleep.

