**APPENDIX B. Jaw Functional Limitation Scale-20（JFLS-20）**

For each of the items below, please indicate the level of limitation **during the last month**. If the activity has been completely avoided because it is too difficult, then circle '10'. If you avoid an activity for reasons other than pain or difficulty, leave the item blank.

|  |  | No  limitation | | | | | Severe  limitation | | | | | |
| --- | --- | --- | --- | --- | --- | --- | --- | --- | --- | --- | --- | --- |
| 1. | Chew tough food | 0 | 1 | 2 | 3 | 4 | 5 | 6 | 7 | 8 | 9 | 10 |
| 2. | Chew hard bread | 0 | 1 | 2 | 3 | 4 | 5 | 6 | 7 | 8 | 9 | 10 |
| 3. | Chew chicken (e.g., prepared in oven) | 0 | 1 | 2 | 3 | 4 | 5 | 6 | 7 | 8 | 9 | 10 |
| 4. | Chew crackers | 0 | 1 | 2 | 3 | 4 | 5 | 6 | 7 | 8 | 9 | 10 |
| 5. | Chew soft food (e.g., macaroni, canned or soft fruits, cooked vegetables, fish) | 0 | 1 | 2 | 3 | 4 | 5 | 6 | 7 | 8 | 9 | 10 |
| 6. | Eat soft food requiring no chewing (e.g.,mashed potatoes, apple sauce, pudding, pureed food) | 0 | 1 | 2 | 3 | 4 | 5 | 6 | 7 | 8 | 9 | 10 |
| 7. | Open wide enough to bite from a whole apple | 0 | 1 | 2 | 3 | 4 | 5 | 6 | 7 | 8 | 9 | 10 |
| 8. | Open wide enough to bite into a  sandwich | 0 | 1 | 2 | 3 | 4 | 5 | 6 | 7 | 8 | 9 | 10 |
| 9. | Open wide enough to talk | 0 | 1 | 2 | 3 | 4 | 5 | 6 | 7 | 8 | 9 | 10 |
| 10. | Open wide enough to drink from a cup | 0 | 1 | 2 | 3 | 4 | 5 | 6 | 7 | 8 | 9 | 10 |
| 11. | Swallow | 0 | 1 | 2 | 3 | 4 | 5 | 6 | 7 | 8 | 9 | 10 |
| 12. | Yawn | 0 | 1 | 2 | 3 | 4 | 5 | 6 | 7 | 8 | 9 | 10 |
| 13. | Talk | 0 | 1 | 2 | 3 | 4 | 5 | 6 | 7 | 8 | 9 | 10 |
| 14. | Sing | 0 | 1 | 2 | 3 | 4 | 5 | 6 | 7 | 8 | 9 | 10 |
| 15. | Putting on a happy face | 0 | 1 | 2 | 3 | 4 | 5 | 6 | 7 | 8 | 9 | 10 |
| 16. | Putting on an angry face | 0 | 1 | 2 | 3 | 4 | 5 | 6 | 7 | 8 | 9 | 10 |
| 17. | Frown | 0 | 1 | 2 | 3 | 4 | 5 | 6 | 7 | 8 | 9 | 10 |
| 18. | Kiss | 0 | 1 | 2 | 3 | 4 | 5 | 6 | 7 | 8 | 9 | 10 |
| 19. | Smile | 0 | 1 | 2 | 3 | 4 | 5 | 6 | 7 | 8 | 9 | 10 |
| 20 | Laugh | 0 | 1 | 2 | 3 | 4 | 5 | 6 | 7 | 8 | 9 | 10 |

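### Three secondary outcomes (PSQI, JFLS-20, jaw movement) have scoring or recording rules that, taken literally, turn usable findings into missing values

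*Combined protocol and SAP*

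**What the plan says.** **JFLS-20.** SAP 8.3.1.2.2 (same text in protocol 8.2.5) states that "non-zero responses that are the same within a subscale were regarded as invalid and recoded to" missing. The rule is limited to non-zero answers, so a subscale answered 0 throughout is kept. For the total built from the subscales: "Note that all 3 subscale scores must be present in order to compute the global score in this manner". The limits on missing items are: "short form, 2 items missing allowed; mastication, 2 items missing allowed; mobility, 1 item missing allowed; and communication, 2 items missing allowed". The form (SAP Appendix B, protocol Appendix D) instructs: "If the activity has been completely avoided because it is too difficult, then circle '10".

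**PSQI.** SAP Table 4 and protocol Table 6 give the same bands. For latency, after a sum of 0 scores 0, the next line is "IF Q5a + Q2new > 1 and < 2, THEN set value to 1"; for daytime dysfunction it is "IF Q8 + Q9 > 1 and < 2, THEN set value to 1". The next bands run from 3 to 4 and from 5 to 6 in the same form. The tables state a maximum of 3 per component and 21 in total.

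**Jaw movement.** Protocol 8.2.3, in its paragraph on lateral and protrusive movement, says: "If the patient cannot perform a movement, indicate this on the recording form by leaving the section blank". SAP 8.3.1.1.2 does not repeat this and offers no other rule.

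**Missing data.** SAP 8.2 describes multiple imputation (10 sets) for weekly pain intensity. SAP 8.3.2 says the continuous secondary outcomes are analysed like the primary one and gives no rule for scores that are missing because of the scoring itself.

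**The concern.** All three measures are named week-4 secondary outcomes and week-8 exploratory outcomes. In each case the rule, followed to the letter, leaves no value where the patient gave an answer or showed a finding, and whether that happens depends on the answer or finding itself. A patient with any latency or daytime problem would have no PSQI total. A patient who scores 10 on every mouth-opening item, as the form asks of someone avoiding all four activities, would have no mobility subscale. A patient who cannot move the jaw sideways would look the same as one who was not examined. With 30 patients per arm, a handful of such losses would be noticeable.

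**Working it through.** **1. PSQI two-item components.** Inputs: the bands in SAP Table 4. The top band ends at 6, so each item runs 0 to 3, giving 4 × 4 = 16 answer pairs with whole-number sums.

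| Sum | Answer pairs | Score as printed | Score with inclusive bounds |
|---|---|---|---|
| 0 | 1 | 0 | 0 |
| 1, 2 | 2 + 3 = 5 | none | 1 |
| 3, 4 | 4 + 3 = 7 | none | 2 |
| 5, 6 | 2 + 1 = 3 | none | 3 |

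No whole number lies strictly between 1 and 2, 3 and 4, or 5 and 6. As printed, 1 of 16 pairs is scored; with inclusive bounds, 16 of 16.

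**2. PSQI maximum.** Stated: 7 × 3 = 21. As printed, latency and daytime dysfunction can only equal 0, so the maximum is 5 × 3 + 2 × 0 = 15. The plan's own figure is not reproduced; with inclusive bounds it is.

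**3. PSQI exact cut-points.** As printed, these also have no band: latency of 0, 15, 30 or 60 minutes; sleep of 5, 6 or 7 hours; efficiency of 65, 75 or 85%; disturbance sums of 1, 9 or 18. Making every bound inclusive is not enough, because latency 15/30/60, duration 5/6/7, efficiency 65/75/85 and disturbance 9/18 would then fall in two bands at once.

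**4. JFLS-20: which scores are lost.** The 8-item score uses items 1, 3, 6, 10, 11, 12, 13 and 19, with 2 missing allowed.

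| Flat non-zero subscale | Items recoded | Of these, in the 8-item score | 8-item score | Three-subscale total |
|---|---|---|---|---|
| Mastication (1-6) | 6 | 3 (1, 3, 6) | lost | lost |
| Vertical mobility (7-10) | 4 | 1 (10) | survives | lost |
| Verbal and emotional expression (13-20) | 8 | 2 (13, 19) | survives | lost |

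**5. JFLS-20: how often.** The documents give no JFLS-20 distribution, so this is assumption only. Model for the four mobility items: latent level normal with SD 1.5 and mean 0.8 to 4, truncated to 0-10; each item is the level plus noise, rounded.

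- Equal item difficulty: flat non-zero rows in 9-16% of patients per visit at noise SD 0.5, 3-5% at 0.8, and 1-2% at 1.2.
- Item offsets +1, +0.5, -0.5, -1: 0.2-0.9% over the same settings.
- Item offsets +2, +1, -1, -2: at most 0.06%.

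On 60 patients, 0.9% is 60 × 0.009 = 0.5 patients and 16% is 60 × 0.16 = 9.6 patients per visit. At an assumed mean of 8, equal difficulty gives 4-23% for this subscale.

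**6. JFLS-20: who is lost.** In the equal-difficulty model at mean 0.8 and noise SD 0.5, dropped patients average 1.8 on the latent scale against 1.0 for those kept. At mean 4 the two groups are almost equal (about 4.05 against 4.00). At the low mean, 76-78% of the deleted rows are flat 1s or 2s, so the gap there comes mainly from sparing flat zeros.

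**7. Jaw movement.** No arithmetic applies. Protocol 8.2.3 uses a blank to mean inability, and a blank is also what an unmeasured item leaves. Both documents say protrusion is negative when the lower incisors cannot pass the upper ones, and the examination form has a field for this, so 0 mm is not the bottom of that scale.

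**The case against.** **PSQI.** Printed bands from 1 to 2, 3 to 4 and 5 to 6 make sense only if the signs were once underlined, and text extraction loses underlining. The tables' own maximum of 21 confirms an inclusive meaning. This stands: a reader might infer that the trial will actually lose the PSQI total of nearly every patient, and the documents do not support that. That the ≥ sign survives in SAP Table 3 does not settle it, since an underlined sign is encoded differently. The text on the total, "The global score < 5 associated with good sleep quality while > 5 associated with poor sleep quality", leaves a score of exactly 5 unclassified, but the PSQI is analysed as a mean change, so this cut feeds no endpoint.

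**JFLS-20.** The recode is a pre-specified validity screen with a stated reason: under item response theory, identical non-zero answers should be very rare. The mobility items range from biting a whole apple to drinking from a cup, so equal difficulty is doubtful, and modest offsets bring the rate below 1%. This stands for the size. It does not explain why the form's own instruction to mark 10 should yield an invalid row, or why flat zeros are exempt. A reader might also infer a biased treatment comparison; the rule applies alike in both arms and no between-arm bias is shown.

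**Jaw movement.** This is a recording instruction in the protocol, not an SAP scoring rule, and the exclusion of locking and limited-opening disc displacement should make it infrequent. Both points stand; the ambiguity of the blank remains.

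**Imputation.** Analysis like the primary one could be read as extending multiple imputation to these scores. The text names only weekly pain, and imputation would in any case replace answers that patients gave.

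**Conclusion.** The point holds for secondary and exploratory outcomes only.

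- **PSQI:** certain as printed (maximum 15 against 21; 1 of 16 answer pairs scored in each of two components), but conditional on the source table carrying the same strict signs.
- **JFLS-20:** the recode is explicit and can remove a severely limited patient's subscale and three-subscale total; the 8-item score survives a flat mobility row. The size is unknown: under 1% to about 16% of patients per visit for mean limitation 0.8 to 4, depending on assumed item difficulty and noise. A large loss of change scores is a tempting inference from the upper end, but it rests on equal item difficulty, which the documents do not support.
- **Jaw movement:** inability cannot be told from not measured; the frequency is not given and is probably low.

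**What to change.** 1. **PSQI:** check the source of SAP Table 4 and protocol Table 6. If the signs are strict, rewrite both with inclusive, gap-free, non-overlapping bands: sums of 1-2, 3-4 and 5-6 score 1, 2 and 3, and each exact cut-point is assigned to one band only.
2. **JFLS-20:** keep flat non-zero responses in the main analysis, flag them, report their number by arm and visit, and exclude them only in a sensitivity analysis. State which global score is the analysed total.
3. **Jaw movement:** add a separate code for inability to perform the movement and pre-specify how it is analysed. Do not impose 0 mm, because protrusion can be negative.
4. State the missing-data method for these secondary scores.

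The cost is wording, scoring code and one form field. The downside is that a few careless JFLS-20 responders stay in the main analysis; the sensitivity analysis shows whether they matter.

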##### 8.3.1.2.3. Depression Anxiety Stress Scales 21 (DASS-21)

The DASS is a set of three self-report scales designed to measure the negative emotional states of depression, anxiety and stress. The DASS was constructed not merely as another set of scales to measure conventionally defined emotional states, but to further the process of defining, understanding, and measuring the ubiquitous and clinically significant emotional states usually described as depression, anxiety and stress. Each of the three DASS scales contains 7 items, divided into subscales with similar content. The Depression scale (item 3,5,10,13,16,17,21) assesses dysphoria, hopelessness, devaluation of life, self-deprecation, lack of interest/involvement, anhedonia, and inertia. The Anxiety scale (item 2,4,7,9,15,19,20) assesses autonomic arousal, skeletal muscle effects, situational anxiety, and subjective experience of anxious affect. The Stress scale (item 1,6,8,11,12,14,18) is sensitive to levels of chronic non-specific arousal. It assesses difficulty relaxing, nervous arousal, and being easily upset/agitated, irritable/over-reactive and impatient. Subjects are asked to use 4-point severity/frequency scales to rate the extent to which they have experienced each state over the past week. Scores for Depression, Anxiety and Stress are calculated by summing the scores for the relevant items. To calculate comparable scores with full DASS, each seven-item scale was multiplied by two. Participants were asked to rate how many of each of the items (in the form of statements) applied to them over the past week, with 0=did not apply to me at all to 3=applied to me very much, or most of the time. The higher the score, the more severe the emotional distress was.

